## Abstract

**Background:**

Falls are the leading cause of unintentional injury and injury-related death among older people. In addition to physical activity, vitamin D also may affect balance and neuromuscular function. Low serum 25-hydroksivitamin D level increases the risk of bone loss, falls and fractures. Thus, an appropriate exercise program and sufficient vitamin D intake may significantly improve not only functional balance, but also balance confidence. Balance represents a complex motor skill determined by reaction time, muscle strength, and speed and coordination of movement.

**Methods/Design:**

A 2-year randomized double-blind placebo-controlled vitamin D and open exercise trial of 409 home-dwelling women 70 to 80 years of age comprising four study arms: 1) exercise + vitamin D (800 IU/d), 2) exercise + placebo, 3) no exercise + vitamin D (800 IU/d), 4) no exercise + placebo. In addition to monthly fall diaries, general health status, life style, bone health, physical functioning, and vitamin D metabolism will be assessed. The primary outcomes are the rate of falls and fall-related injuries. Secondary outcomes include changes in neuromuscular functioning (e.g. body balance, muscle strength), ADL- and mobility functions, bone density and structure, cardiovascular risk factors, quality of life and fear of falling.

**Discussion:**

The successful completion of this trial will provide evidence on the effectiveness of exercise and vitamin D for falls reduction.

**Trial Registration:**

ClinicalTrial.gov -register (NCT00986466).

## Background

The rising population of the elderly over the next few decades will be accompanied by an increase in the number of people with disease and chronic illness. Older people are less resistant to injury, whether from physiological events (e.g. heart attack) or environmental trauma (e.g. bone fracture), as well as to infection [1]. Health maintenance for aging people over their life span through exercise and proper nutrition contribute to lifelong wellbeing [2].

Osteoporosis, with the main outcome problem of fractures, is a multifactorial disease characterized by low bone mineral density (BMD) and decreased bone strength. Often these people also have neuromuscular deficiencies resulting in an increased risk of falling. Falls are the leading cause of unintentional injury and injury-related death among older adults. Approximately 30% of community living people aged 65 years or older fall every year the rate being clearly higher in institutions. Although less than one fall out of 10 results in a fracture, 20% of fall incidents require admissions to hospital [3-5]. Since the propensity to fall increases the risk of fracture and other injuries considerably, falls prevention is widely considered to be the most essential element when planning effective injury and fracture prevention programs for the elderly population [3,6-8].

Preventing falls and injuries among older adults is challenging. However, there is strong high-quality evidence from randomized controlled trials and subsequent systematic reviews and meta-analyses that regular strength and balance training for elderly adults living in the community can reduce the risk of both noninjurious and injurious falls by 15-50% [3,7,9,10]. Randomized controlled trials indicate that not only individually tailored training but also untargeted group exercise programs are effective in preventing falls [11-14], particularly if the training program includes Tai Chi or other exercises which challenge balance [14-16] and improve lower limb muscle strength [8,10]. Thus, it seems prudent to recommend regular weight-bearing and other exercises for community-dwelling older adults, not only to maintain their musculoskeletal health, but also to help them stay safely on their feet [17-19].

Hypovitaminosis D is becoming a widespread concern around the world regardless of the latitude. Serum 25-hydroxy vitamin D (S-25-OHD) concentration, which is the best indictor of vitamin D status, has been shown to decrease in elderly Finnish women in winter [20,21]. It has been estimated that ambulatory elderly women require on average 18 μg vitamin D per day to maintain adequate vitamin D level (that is, S-25-OHD above 50 nmol/L) during winter. Inadequate intakes of vitamin D and calcium lead to reduced calcium absorption, higher bone turnover and increased bone loss and risk of fractures [22-25]. Even more important may be the finding that S-25-OHD level is inversely associated with falls [24,26-28]. In randomized controlled trials the incidence of falls was almost halved and musculoskeletal function improved among elderly people with a combination of vitamin D and calcium compared with calcium supplement alone [29,30]. Falling may, at least partly, be a consequence of impaired neuromuscular function associated with vitamin D deficiency, since abnormal motor performance, increased body sway, and quadriceps weakness have been reported in those with low vitamin D status. Vitamin D receptors are known to be present in muscle tissue. Furthermore, the number of fast type II muscle fibers decreases with age, and these fibers are the first to be recruited in balance perturbation to avoid falling [31,32].

In prevention of fractures of elderly people, the focus should be shifted from treating low BMD to improving muscle strength and the neuromuscular co-ordination to avoid falls, since most fractures are a direct consequence of falling [33]. Although a recently published metaanalysis found little evidence that current multifactorial falls prevention programs could prevent falls and related injuries [34], it must be kept in mind that a great majority of fall-prone elderly adults has more than one risk factor for falls. Furthermore, fear of falling may restrict habitual physical activity and lead to declined functional ability [19,35,36].

As noted above, randomized controlled trials suggest that exercise may effectively improve many factors affecting falling, such as muscle strength, flexibility, balance, coordination, proprioception, reaction time and gait [37-41]; thus reducing the risk of falling [3,7-9,42]. Regular moderate to vigorous exercise is also associated with reduced number of fractures [18,43,44]. Also vitamin D has been proposed to protect against falls and fractures [27]. Thus, it is well justified to study the separate and combined effects of exercise and vitamin D in prevention of falls and related injuries.

Although there is evidence that both exercise and vitamin D by themselves can benefit neuromuscular and cognitive function, and thus contribute to reduced risk of falls; these two factors have not previously been evaluated in combination. In this paper, we describe the design of such a study.

## Methods/Design

### Study aims, design and setting

The present study is a four-arm randomized, double-blind placebo-controlled vitamin D and open exercise intervention trial where community-dwelling, independently living Finnish women aged 70 to 80 years are randomized to receive either vitamin D 800 IU (20 μg/d) or placebo, and to participate in either supervised exercise or non-exercise group for 24 months (DEX study).

The primary aim of this study is to investigate the effects of exercise and vitamin D supplementation, alone or in combination, on reducing falls and fall-related injuries.

### Ethical consideration

The study protocol has been approved by the Ethics Committee of the Tampere University Hospital, Tampere, Finland (R09090). Each participant provided her written informed consent prior to randomization. The study protocol is registered in the ClinicalTrial.gov - register (NCT00986466).

### Outcomes

The primary outcome of the study is the rate of falls and fall-related injuries. Changes in neuromuscular functioning (e.g. body balance, muscle strength), ADL- and mobility functions, bone health, fractures, cardiovascular risk factors, health-related quality of life, fear of falling, depression (WHO-5), cognition (Mini-mental State examination, MMSE) and rate of institutionalization will be analyzed as the secondary outcomes.

### Sample size consideration

The sample size and power calculations have been estimated for the primary outcome of this study, i.e., the rate of falls. We hypothesized that there will be a 30% difference in the rate of falls between the treatment groups (vitamin D vs. placebo, and exercise vs. non-exercise). The number of women in each group is based on the expectation that the intervention programme (exercise or vitamin D treatment) will reduce the incidence rate of falls by 30% during the two years intervention and the between-group difference will be detected for a given significance level of 0.05 with a statistical power of 80% with a mean treatment time of 1.5 years. The baseline incidence was assumed to be 67 falls per 100 person-years. Accordingly 260 participants needed to be recruited into the study (130 exercisers and 130 non-exercisers, 65 in each group with vitamin D supplement). However, in order to eliminate the role of chance in detecting the possible interaction of vitamin D and exercise, a total number of 400 subjects (100 subjects in each group) were recruited into the study.

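### The 260 women stated for 80% power do not follow from the listed inputs: a two-sided Poisson comparison at 1.5 years needs about 295–300, and 260 give about 75%

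*Protocol article*

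**What the plan says.** All the inputs stand in one paragraph of the Protocol article, Sample size consideration.

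- Effect: the authors hypothesise that "there will be a 30% difference in the rate of falls between the treatment groups (vitamin D vs. placebo, and exercise vs. non-exercise"; the programme "will reduce the incidence rate of falls by 30% during the two years intervention".
- Error rates and time: the difference is to be "detected for a given significance level of 0.05 with a statistical power of 80% with a mean treatment time of 1.5 years".
- Rate: "The baseline incidence was assumed to be 67 falls per 100 person-years".
- Result: "Accordingly 260 participants needed to be recruited into the study (130 exercisers and 130 non-exercisers"), with 65 women on each side taking vitamin D.

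The paragraph then says that 400 women, 100 per arm, were recruited, and gives the possible interaction of the two treatments as the reason. The Randomization section reports 409 women randomised. The Plan of analysis names Poisson regression in a 2 × 2 factorial layout, comparing the two exercise groups and the two vitamin D groups. The paragraph states no sidedness, no dropout rate and no allowance for extra-Poisson variation.

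**The concern.** The paragraph prints a full set of inputs and presents 260 as their consequence, so the figure can be checked without any further document. It fails the check by about 35–40 women under the usual two-sided convention.

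The second issue lies in the factorial layout. Each comparison is between two halves of the trial, and half of each side also receives the other treatment. If that treatment also works, both sides have lower fall rates, fewer falls are observed, and the main effect is harder to detect.

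What is at stake is the stated justification. The text attributes the whole step from 260 to 400 to the interaction, so a reader would take 140 women as surplus to the main effects. On the listed inputs, a good part of that surplus is needed for the main effects themselves.

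**Working it through.** **Inputs** (Sample size consideration): comparator rate r0 = 0.67 per person-year; r1 = 0.70 × 0.67 = 0.469; difference 0.201; time t = 1.5 years per woman; 130 per side; power 80%; alpha 0.05, taken as two-sided (assumption). Poisson variance is used because the Plan of analysis names Poisson regression.

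**1. Attempt to reproduce 260.**
Person-years per side = (z₀.₉₇₅ + z₀.₈₀)² × (r0 + r1) / (r0 − r1)²
= (1.96 + 0.8416)² × 1.139 / 0.201²
= 7.849 × 1.139 / 0.0404 = 221.3.

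221.3 / 1.5 = 147.5, so 148 women per side and about 295–296 in total. The stated figure is not reproduced. Other standard formulas with the same inputs:

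| Method (two-sided, 1.5 years) | Total N for 80% | Power at 130 per side |
|---|---|---|
| Rate difference | 296 | 74.9% |
| Log rate ratio | 300 | 74.4% |
| Square-root scale | 294 | 75.2% |
| Schoenfeld events | 290 | 75.7% |
| Freedman events | 298 | – |

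**2. Power at 260.** Person-years per side = 130 × 1.5 = 195. Expected falls are 195 × 0.67 = 130.7 and 195 × 0.469 = 91.5. Standard error of the rate difference = √(1.139 / 195) = 0.0764, and 0.201 / 0.0764 = 2.63. Power = Φ(2.63 − 1.96) = 0.749. A simulation of 400,000 trials with the log-ratio test gave 75.0%.

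**3. One-sided 0.05.** (1.645 + 0.8416)² = 6.183; 6.183 × 1.139 / 0.0404 = 174.3 person-years per side; / 1.5 = 116.2. The total is about 232–236 by the rate-difference, log and square-root formulas, and power at 260 is about 84%. This does not give 260 either.

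**4. Both effects real** (multiplicative, no interaction, 0.67 as the rate with neither treatment).
Comparator side: (0.67 + 0.469) / 2 = 0.5695. Treated side: 0.70 × 0.5695 = 0.3987.
Person-years per side = 7.849 × 0.9682 / 0.1709² = 260.3; / 1.5 = 173.6 (log scale 175.4). The total is about 347–351.
Power at 195 person-years: √(0.9682 / 195) = 0.0705; 0.1709 / 0.0705 = 2.42; Φ(2.42 − 1.96) = 0.679, or about 68%.

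**5. The trial as recruited** (two-sided, 1.5 years, Poisson).

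| Women | One effect | Both effects |
|---|---|---|
| 400 (200 per side) | 90% | 85% |
| 409 (204.5 per side) | 91% | 86% |

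For 409: 204.5 × 1.5 = 306.75 person-years per side. One effect: 0.201 / √(1.139 / 306.75) = 3.30, Φ(1.34) = 0.91. Both effects: 0.1709 / √(0.9682 / 306.75) = 3.04, Φ(1.08) = 0.86.

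**6. What would give about 260.** Only inputs that the paragraph does not state: a mean of 1.70 years (221.3 / 130); 2 years with both effects real (260.3 / 2 = 130.2 per side); 2 years with 15% dropout (222 / 0.85 ≈ 262); or one-sided alpha with 10% dropout (234 / 0.90 = 260).

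**The case against.** **260 was not the number used.** This is the strongest point. The same paragraph moves on to 400, and 409 were randomised; power at either number exceeds 80% on the listed inputs, with one effect or both. A reader might infer from the 75% or 68% that the trial is underpowered. Under Poisson variance the document does not support that. The fault is in the derivation of 260.

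**Sidedness is not stated.** That is correct, and under a one-sided test 260 women exceed 80% power for a single effect. The 75% therefore rests on the two-sided convention. But 260 is still not what a one-sided calculation returns.

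**Treatment time may differ from monitored time.** The Plan of analysis divides falls by the time monitored, and the intervention lasts 24 months. With 2 monitored years, 260 women would give about 86% for one effect. However, 1.5 years is the only duration the power statement attaches to the 80%, and 2 years alone would need about 222 women, so this does not explain 260 without a further input.

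**The 68% is conditional.** If 0.67 is read as the rate of the whole comparator half, there is no further dilution and the figure does not apply. A reader might also conclude that the authors overlooked the other factor. This cannot be shown: both effects with 2 years also lead to about 130 per side.

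**Overdispersion.** A reader might want a specific lower power for overdispersed fall counts. The document gives no variance figure, and a condensed article may leave this to the full plan, so only the direction can be stated. Likewise, the absence of a stated power for 409 is an omission in a short article and is not itself an error.

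**Conclusion.** The point holds as an arithmetic error in the stated justification. With 0.67 against 0.469 falls per person-year, Poisson variance, two-sided 0.05 and 1.5 years per woman, 80% power needs about 295–300 women, and 260 give about 75%. No standard formula tried on the stated inputs returns 260, two-sided or one-sided.

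The figures of about 68% power and 347–351 women are a sensitivity result. They require both 30% effects to be real and multiplicative without interaction, and 0.67 to be the rate with neither treatment.

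The consequence for the trial is limited, because the 409 randomised have about 86–91% power under Poisson variance. What is misleading is that the increase over 260 is credited wholly to the interaction: on the listed inputs, about 35–40 of those extra women are needed for a single main effect, and about 90 if both factors work.

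**What to change.** In Sample size consideration, do one of two things:

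- replace the statement that 260 women give 80% power with about 295–300 women at a mean of 1.5 years, two-sided, and about 350 if both factors are effective (multiplicative, no interaction); or
- keep 260 and state the sidedness and the person-time per woman that produced it, with any dropout allowance.

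In either case, add that the 409 women randomised give about 86–91% power for each main effect under Poisson variance at 1.5 years (two-sided), and that this would be lower if fall counts are overdispersed. Amend the sentence on the increase to 400 so that it does not credit the whole increase to the interaction.

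The cost is one corrected paragraph. No further recruitment and no change to the analysis follow from it.

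### One hundred women per arm does not secure detection of an exercise-by-vitamin D interaction; for one as large as a main effect, power is about 28-40%

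*Protocol article*

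**What the plan says.** The Sample size consideration section of the Protocol article sizes the trial on two main-effect contrasts: "We hypothesized that there will be a 30% difference in the rate of falls between the treatment groups", specified as "vitamin D vs. placebo, and exercise vs. non-exercise". The inputs are a 30% lower fall rate, 80% power, "a given significance level of 0.05", and "a mean treatment time of 1.5 years". The control rate is also given: "The baseline incidence was assumed to be 67 falls per 100 person-years". These lead to 260 women, 130 per margin and 65 per arm.

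The section then gives one reason for exceeding that number: "in order to eliminate the role of chance in detecting the possible interaction of vitamin D and exercise, a total number of 400 subjects", that is, 100 per arm. It names no interaction size and no interaction power. The Randomization section reports that 409 women were allocated. The Plan of analysis describes a 2 × 2 factorial Poisson analysis that estimates a rate ratio for each margin.

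**The concern.** The sentence attributes a property to the sample size. Taken literally, it is impossible. Taken generously, it says that 100 women per arm makes detection of an interaction dependable. That is doubtful on general grounds: in a balanced 2 × 2 design on the log scale, the interaction contrast has about four times the variance of a main effect, while the sample was raised only by a factor of 400/260 = 1.54.

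What is at stake is how the interaction result can be read. Someone who relies on the stated rationale may give a non-significant interaction test more weight than it can carry. The two marginal rate ratios are also easiest to interpret when there is no material interaction.

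**Working it through.** **Inputs from the Sample size consideration section:** control rate 0.67 per person-year; rate ratio 0.70 for each factor; 1.5 years per woman; alpha 0.05; 80% power; 260 women for the main effects, 400 recruited.

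**Assumptions not in the article:** a two-sided test; an interaction ratio R of 0.70 or 1/0.70, equal in size to a main effect; Poisson variance unless stated otherwise.

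**1. The plan's own figure.** For a main effect, n per margin = (1.960 + 0.842)² × (1/0.67 + 1/0.469) / (1.5 × (ln 0.70)²) = 7.849 × 3.625 / (1.5 × 0.1272) ≈ 149, or about 300 in total. The stated 260 is not reproduced with 1.5 years; it gives about 74% power. This is a separate matter. Step 3 therefore also takes the stated 80% at 260 as given.

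**2. Interaction power from the stated rates.** With n women per arm followed for T years:

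SE(ln R) = √[Σ 1/rate / (nT)], summed over the four arms; power = Φ(|ln 0.70|/SE − 1.960), with |ln 0.70| = 0.3567.

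At 100 per arm and 1.5 years, nT = 150. The first pattern, for example, gives SE = √(10.11/150) = 0.260 and power = Φ(0.3567/0.260 − 1.960) = Φ(−0.59) = 28%.

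| Cell rates (neither, one, other, both) | Σ 1/rate | SE | Power, 65/arm | Power, 100/arm | Power, 100/arm, 2.0 years | Women/arm for 80% | Ratio detectable at 80%, 100/arm |
|---|---|---|---|---|---|---|---|
| 0.67, 0.469, 0.469, 0.230 (extra synergy) | 10.11 | 0.260 | 20% | 28% | 35% | 416 | 0.48 |
| 0.67, 0.469, 0.469, 0.328 (variance at no interaction) | 8.80 | 0.242 | 22% | 31% | 40% | 362 | 0.51 |
| 0.67, 0.469, 0.469, 0.469 (no added benefit of both) | 7.89 | 0.229 | 24% | 34% | 43% | 324 | 0.53 (1/0.53 in this direction) |
| 0.67, 0.67, 0.67, 0.469 (only both together work) | 6.61 | 0.210 | 28% | 40% | 50% | 272 | 0.56 |

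Except in the 2.0-year column, T is 1.5 years. Women per arm = 7.849 × Σ 1/rate / (1.5 × 0.1272). Detectable ratio = exp(−2.802 × SE), with the variance held at the row's cell rates.

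If both main effects hold and the variance is evaluated at the detectable ratio itself, R = 0.45 gives Σ 1/rate = 12.53, SE = 0.289 and power 79%. The detectable ratio is then about 0.45 or, in the opposite direction, about 1.87.

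**3. Scaling from the stated 80% at 260.** Doubling the SE for the interaction, power at 400 = Φ((2.802/2) × √(400/260) − 1.960) = Φ(−0.22) = 41%. The same rule puts the requirement for 80% at 4 × 260 = 1,040 women.

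**4. Overdispersion (assumed).** With a negative binomial dispersion of 0.3 to 1.0, power at 100 per arm and 1.5 years is 19-33%. With a variance-to-mean ratio of 2, it is 16-20% for the first and third patterns.

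**5. The 409 randomized.** At 102.25 per arm the Poisson range is still 28-40%.

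**6. What the extra women do buy.** Main-effect power at 400 and 1.5 years is about 90%, or about 85% if the control margin is diluted by the other effective treatment. At 260 it is 74% and 67% by the same formulas.

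**7. Combined arm versus double placebo.** |ln(0.3283/0.67)| = 0.713; SE = √[(1/0.67 + 1/0.3283)/150] = 0.174; power = Φ(4.10 − 1.96) = 98%. With a variance-to-mean ratio of 2 it is about 83%.

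**The case against.** The fairest defence is that the phrase is loose, that it means reducing chance rather than removing it, and that no power figure is claimed. The interaction ratio of 0.70 is an assumption of this review, not an input of the plan, so no single power figure can be held against the article. The larger sample does no harm: it narrows every estimate, and the formal calculation concerns the main effects. All of this stands, and it is why the result is given as a range and the severity is limited. It does not rescue the sentence. The reason given for the increase is the interaction, and every variant examined falls well short of 80%. Nor is this a detail left to a fuller document, because the article makes the claim affirmatively.

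Two stronger readings may tempt a reader, and the article supports neither.

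- **That the trial will treat a non-significant interaction as proof of independent action.** The Plan of analysis sets no such rule and does not make the marginal analysis conditional on an interaction test. Misreading is a foreseeable risk, not a planned inference.
- **That the aim of studying the treatments together is undermined.** That aim can be met by comparing the combined arm with double placebo, which needs no interaction contrast and has about 98% power on the same Poisson inputs.

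**Conclusion.** The point holds as an overclaimed rationale of moderate severity. The stated reason for going from 260 to 400 describes a property that the design does not have. For an interaction as large as the hypothesised main effect, power is about 28-40% at 1.5 years under Poisson variance. It is about 41% if the plan's own 80% at 260 is accepted and scaled, at most about 50% with two full years for every woman, and lower with overdispersion. Dependable detection would need an interaction ratio of about 0.45-0.56, or about 270-415 women per arm. The exact figures rest on the assumed ratio and cell rates; the conclusion does not change across them. The main-effect analyses, and the choice of 400 as such, are not put in question by this point.

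**What to change.** Replace the sentence on eliminating chance with text along these lines:

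> The sample was increased to 400 women (100 per arm), which mainly raises power and precision for the two main effects. For an assumed interaction ratio of 0.70 or 1/0.70, with 0.67 falls per person-year, 30% main effects, 1.5 years of exposure and two-sided 0.05, power is about 28-40% under Poisson variance and lower with overdispersion. The interaction ratio will be reported with its 95% CI as exploratory, and a non-significant test will not be taken as evidence of no interaction.

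The smallest ratio detectable with 80% power (about 0.45-0.56) could be stated instead of the power range, with the same assumptions.

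The cost is wording only. Recruitment is complete according to the Discussion, and the sample, the data collection and the primary analysis are unchanged. A stated property of the design becomes less favourable. The change is best made before results are known.
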